## Methods and design

This study is a randomized controlled pragmatic trial conducted in three ordinary child welfare agencies in and around Oslo, Norway. The agencies differ in size, organizational structure, and demographic characteristics. Selected practitioners at each site have received training in the EAS intervention. Practitioner selection to EAS training was mostly a matter of practicality (i.e., half of the practitioners in a team, geographic area, or unit were selected by their managers to receive training). Participating families are recruited individually at each site and randomized either to an EAS-trained practitioner or to a practitioner not trained in EAS who is delivering regular child welfare support measures (BAU). EAS is delivered over the course of 6 months. Participants are assessed before and immediately after EAS, and at follow-up, 6 months after the end of the intervention. The schedule of recruitment, allocation, assessments, and experimental conditions is provided in Fig. 1. The Standard Protocol Items: Recommendations for Interventional Trials (SPIRIT) checklist is provided as Additional file 1.

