*Additional strategies based on the intervention, context assessment, and knowledge exchange in co-creation teams*							
Make intervention dynamic and flexible	Dissemination strategy	Synthesis and translation system	Common elements of effective interventions have been used as basis for the intervention components to enable dynamic and flexible delivery	Systematic review, common elements analysis	To utilize the best available empirical evidence and improve intervention feasibility, appropriateness, and acceptability at all levels	Synthesis, co-creation	Feasibility, appropriateness, acceptability, fidelity
Train champions	Capacity-building strategy	Support system and delivery system	Champions have received additional training in the intervention, knowledge translation, implementation strategies, and behavior change	7-h group training	Build local implementation and coaching capacity on provider and organizational levels	Implementation	Feasibility, fidelity, reach
Use ongoing coaching	Capacity-building strategy and integration strategy	Delivery system and support system	Intervention practitioners receive group coaching from external implementation team and champions. Individual coaching is provided upon request or in cases of fidelity drift	Bimonthly from external implementation team, monthly from champions, and individually on request (registered)	Promote learning and integration of the intervention in practitioners and champions on provider and organizational levels	Implementation, evaluation, sustainment	Fidelity, reach, perceived competence
Use continuous support	Capacity-building and integration strategy	Support system	Group consultations, booster sessions, telephone support, training of new practitioners, recruiters, and champions	Bimonthly meetings with practitioners, recruiters, and champions, 4-h booster session every 6 months, telephone support, visiting support and training on request (registered)	Provide support and boost engagement, implementation quality^c^, and recruitment at the provider and organizational levels	Implementation, evaluation, sustainment	Feasibility, fidelity, reach, perceived competence

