#### Implementation measures

The following implementation measures are used in this study:A monitoring checklist has been developed to measure adherence to core components, dosage, competence in delivery, parent comprehension of core components, adaptations, and user involvement and satisfaction with delivery of intervention components. The checklist is completed by EAS practitioners using smartphones after each intervention session and by parents answering the same questions in telephone interviews after each intervention session (see the section “Monitoring and safety” for more details).An end-of-intervention checklist measures academic support received/given, emergent life events/adverse events, and overall user satisfaction and involvement during the last 6 months (intervention period). It has been developed specifically for this study and is administered at the post-assessment to parents (15 items), children (16 items), and practitioners (20 items) in both conditions. Items are rated on a 4-point scale (“not at all”, “to a small degree”, “to some degree”, “to a large degree”). Each version ends with an open question about any additional information to be answered in free text.Intervention feasibility, acceptability, and appropriateness will be measured using three four-item scales: Acceptability of Intervention Measure (AIM), Intervention Appropriateness Measure (IAM), and Feasibility of Intervention Measure (FIM) [30]. The AIM, IAM, and FIM are completed by the EAS practitioners post-intervention.Organizational readiness for change is assessed using an unpublished questionnaire made by the study authors with 32 items rated on a 5-point scale (ranging from “strongly disagree”, “somewhat disagree”, “unsure”, “somewhat agree”, to “strongly agree”). The questionnaire measures organizational factors, characteristics, needs, and work climate as well as staff characteristics, qualities, and needs. It is administered to all employees at all CWS sites, pre- and post-intervention. Organizational managers answer two additional items measuring organizational resources and opportunities.Organizational climate for implementing evidence-based practice (EBP) is assessed using the Implementation Climate Scale (ICS) [31]. The scale consists of 18 items rated on a 5-point scale (from “not at all” to “very great extent”). The ICS assesses the degree to which there is a strategic organizational climate supportive of EBP implementation. Subscales include focus on EBP, educational support for EBP, recognition for EBP, rewards for EBP, selection (employment) for EBP, and selection (employment) for openness. The ICS is administered to all employees at all CWS sites pre- and post-intervention. It has been validated with practitioners in 32 mental health organizations and 12 child welfare services in the USA [31, 32].Practitioners’ perceived competence in providing academic support is measured using an unpublished questionnaire developed by the study authors. It includes 12 items rated on a 5-point scale ranging from “strongly disagree” (0) to strongly “agree” (5). The questionnaire assesses knowledge and use of competencies relevant to the core components of EAS without using the specific wording of the core components in the EAS handbook. It is administered pre-training and post- intervention to EAS practitioners.CWS employees’ perceptions of the implementation process and the EAS intervention will be gauged by conducting focus group interviews post-intervention. An interview protocol will be prepared based on the IKT-K model and the DAP framework, including questions about the appropriateness and acceptability of EAS. Some of the topics to be discussed in the focus groups will include results from the quantitative data analyses.Semi-structured interviews will be conducted with a selection of participating children and parents after the intervention to learn more about their experiences with EAS. To select families to approach for participation in interviews, a randomization procedure in the Confirmit software will be used. Randomization will be stratified to select families who benefited from the intervention, who did not benefit from the intervention, and families with different ethnicities from each of the three sites.

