#### Randomization

At the time of consent, parents and children are informed that they will be randomly allocated to one of two conditions; one group, the BAU condition, receives regular measures from CWS, whereas the experimental condition receives the EAS intervention in addition to a regular child welfare measure. Blinding is not possible in this study; child welfare practitioners who have received EAS training will exclusively give EAS to study families, and parents and children will most likely understand to which group they have been assigned.

After completing the pre-assessment, participants are automatically randomized to either the intervention group (EAS) or the comparison group (BAU). A computer software (Confirmit) generates a random numbers table to assign random numbers to participants within blocks. A block randomization with a block of 10 is used, and randomization is carried out site-wise. The research coordinator informs the team manager at the site to assign the case to a practitioner with or without EAS training. All edit trails in Confirmit are recorded. Outcome assessors are blinded to allocation. In-depth technical details can be provided upon request.

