#### Comparison condition: business as usual (BAU)

Families allocated to the BAU group are assigned a practitioner without training in EAS. BAU is delivered as described in the “Methods and design” subsection “Comparison condition (business as usual)”.

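### Managers, not chance, formed the two practitioner groups and no practitioner serves both arms, so the effect of EAS cannot be separated from any difference between those groups

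*Protocol article*

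**What the plan says.** On who was trained, the protocol article (Methods and design) states: "Practitioner selection to EAS training was mostly a matter of practicality". It explains that "half of the practitioners in a team, geographic area, or unit were selected by their managers to receive training". It mentions no random draw and no matching of trained with untrained staff.

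On what families are randomised to, the same section says they are "randomized either to an EAS-trained practitioner or to a practitioner not trained in EAS". The Randomization subsection describes a computer-generated allocation by site, in blocks of 10, after the pre-assessment. It then says: "The research coordinator informs the team manager at the site to assign the case to a practitioner with or without EAS training".

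On whether practitioners cross arms, the Randomization subsection says that "child welfare practitioners who have received EAS training will exclusively give EAS to study families". The Procedures subsection on BAU says: "Families allocated to the BAU group are assigned a practitioner without training in EAS". The matching subsection on EAS assigns intervention families to trained practitioners.

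On the target of inference, Aim 2 (Aims and hypotheses) is to evaluate the effects of EAS itself. Statistical analyses specifies an ANCOVA with baseline scores and covariates. The covariates listed in Aims and hypotheses describe the child and family.

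On data about practitioners, Implementation measures says of the readiness questionnaire: "It is administered to all employees at all CWS sites, pre- and post-intervention". The climate scale is given to the same staff at the same times. Perceived competence in academic support is measured in EAS practitioners only.

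**The concern.** Randomising families makes the two arms alike, in expectation, in everything the families bring. It does nothing for what the practitioners bring, because every trained practitioner sits in one arm and every untrained one in the other, and a manager rather than a random draw decided who was trained. Practitioner group and treatment are completely aliased: no practitioner provides a within-person comparison of EAS with BAU, and no chance mechanism makes the two groups comparable on average.

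The protocol article itself indicates that practitioners matter, since its description of the comparison condition says that BAU differs from one practitioner to another. If the selected half differs from the rest in experience, motivation or caseload, the difference goes straight into the estimated effect of EAS. It could inflate or mask that effect. This is a question of bias, separate from the loss of precision that comes from several families sharing a practitioner.

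**Working it through.** **Structure of the comparison.**

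| Element | EAS arm | BAU arm | Balanced by randomisation? |
|---|---|---|---|
| Families | allocated by computer, by site | allocated by computer, by site | yes, in expectation |
| Practitioner pool | selected by managers for training | not selected | no |
| Individual practitioner | assigned by team manager within the arm | assigned by team manager within the arm | no |
| Support given | regular measure plus EAS | regular measure | this is the contrast of interest |

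The separation of the two pools follows from the assignment rule in the Procedures subsections, whichever way the sentence on trained practitioners giving EAS exclusively is read. The estimated contrast is therefore (effect of EAS) + (selected minus unselected practitioners), and the design supplies no information to split the sum.

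**The plan's own yardstick.** Power calculation uses d = 0.65 and 80% power and arrives at 39 families per group. A two-sample t-test at two-sided 0.05, the level given in Statistical analyses, needs 38.14 per group. This rounds up to 39, with power 0.809, so the figure reproduces. The planned 120 families give about 60 per arm.

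**Illustrative size of the bias.** The documents give neither the practitioner share of outcome variance (ICC) nor the gap between the two groups. Both are assumptions here:

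- ICC: 0.05 to 0.10.
- Gap g: 0 to 1 practitioner-level SD, in either direction. With half the practitioners selected, a gap of 1 SD corresponds to a correlation of 0.5 between being selected and the practitioner's contribution (g = 2r).

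With the total outcome SD set to 1, the practitioner-level SD is √ICC, so |bias| = g × √ICC. The chance of declaring a difference when EAS has no effect, with 60 families per arm and clustering ignored, is P(|Z + bias/SE| > 1.96), where SE = √(2/60) = 0.183.

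| ICC | g (absolute) | bias in absolute d | share of 0.65 | chance of a significant result, no EAS effect |
|---|---|---|---|---|
| either | 0 | 0 | 0% | 5% |
| 0.05 | 0.25 | 0.25 × 0.224 = 0.06 | 9% | 6.1% |
| 0.05 | 0.5 | 0.5 × 0.224 = 0.11 | 17% | 9.4% |
| 0.05 | 1.0 | 1.0 × 0.224 = 0.22 | 34% | 23% |
| 0.10 | 0.25 | 0.25 × 0.316 = 0.08 | 12% | 7.2% |
| 0.10 | 0.5 | 0.5 × 0.316 = 0.16 | 24% | 14% |
| 0.10 | 1.0 | 1.0 × 0.316 = 0.32 | 49% | 41% |

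The number of families does not enter the bias formula. It enters only the SE, so recruiting more families leaves the bias where it is.

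**The case against.** The strongest case on the other side has four parts.

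- **No quality gap is shown.** Selection is described as mainly practical and took half of each team, area or unit. Nothing says that managers picked on skill, experience or workload. The most engaged staff were offered champion roles with extra EAS training (Knowledge translation procedure), but the article does not say that champions treat study families. A reader might infer that the arm is confounded with practitioner quality and that a positive result would reflect better practitioners. The documents do not support that: the gap could be zero, or it could favour BAU. This part stands, and it is why the illustration starts at zero and runs both ways.
- **Family randomisation is intact.** A reader might also infer that the team manager's choice of practitioner undermines the allocation. It does not. The computer fixes the arm, and the manager chooses only a person within it, as happens in ordinary service delivery. This part stands too.
- **The trial is pragmatic and open about the selection.** The comparison remains valid for EAS as these agencies delivered it. That is correct, but Aim 2 is worded as the effect of EAS, which is a wider claim.
- **Some relevant data and analyses exist, and a full plan may hold more.** Readiness and climate are to be tested as predictors and moderators, and the end-of-intervention checklist is completed in both conditions. A practitioner table could sit in a document not shown, so its absence is not the point here. The point is the design, which no analysis plan can undo. Testing readiness and climate as predictors or moderators is also not a comparison of practitioners between arms.

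The remedies have limits as well. The first practitioners had finished training and piloting, and recruitment had begun (Intervention; Trial status). The climate scale describes the organisation rather than individual skill. The article does not say that staff surveys can be linked to individual practitioners, or that education or years in service are recorded. These limits reduce what a repair can achieve, but they do not remove the aliasing.

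**Conclusion.** The point holds as a limit on what the trial can attribute to EAS. The arm is completely aliased with a practitioner group formed by managers, so a practitioner difference of unknown size and direction cannot be separated from the effect named in Aim 2. The randomised comparison of families, and its validity for the package as delivered, are not in question.

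With an assumed ICC of 0.05 to 0.10 and an assumed gap of 0 to 1 practitioner-level SD either way, the bias is between 0 and about 0.32 in absolute d, at most 49% of the planned 0.65. These figures show scale only; they are not estimates for this trial.

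A reader might infer that an adjusted analysis agreeing with the main one would clear the matter. It would not, because adjustment for measured scores cannot exclude unmeasured differences between two groups that never overlap.

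**What to change.** 1. **Conclusion.** State the Aim 2 result, without condition, as the effect of EAS as delivered by manager-selected practitioners compared with BAU by the unselected ones. Keep this wording whatever the sensitivity analysis shows.
2. **Description and partial check.** Tabulate by arm the pre-training readiness and climate scores of the treating practitioners, with any background data already held. These surveys went to all staff, and Table 2 (Assess context) places them in the co-creation phase, before training. Add one sensitivity ANCOVA adjusting for them, described as a partial check that cannot remove the aliasing. This needs survey responses linked to practitioners. The article does not state that link, but relating readiness and climate to fidelity and outcomes with only three sites suggests that it is intended. Practitioners who joined later may lack pre-training scores, and the table should say how many.
3. **Later trainees.** Table 2 (Use continuous support) provides for "training of new practitioners, recruiters, and champions". Where more than one practitioner in a team or unit is available for training, choose by lot. This leaves the first selection as it is, and the article gives no number of later trainees, so the gain may be small.

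The cost is a more guarded conclusion, one extra model with the data linkage, and slightly less discretion for managers.

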**Fig. 1 Fig1:**
[figure not shown]
Schedule of enrollment, interventions, and assessments

### Participants

Eligible participants are boys and girls in primary school and their parents, whose family receives support measures from CWS. We plan to recruit 120 children and their parents.

#### Inclusion criteria

The following inclusion criteria must be met:Children in families receiving support measures from municipal CWSBoys and girls in the 1st to 7th grades and their parents/caregiversParents/caregivers who give informed consent. Consent, assent, and the questionnaires are available in Norwegian, English, Arabic, and Somali.

#### Exclusion criteria

The exclusion criteria are as follows:Developmental disabilityParents/caregivers not able to give informed consent due to language restriction (not able to understand Norwegian, English, Arabic, or Somali)One child only from each family can participate

The study also includes managers and practitioners at the local child welfare agencies (*N* = 160), the children’s teachers, and other stakeholders (parents and youths who previously received CWS, youth from user organizations, and local school counselors; estimated *N* = 22) in and around Oslo, Norway.

#### Power calculation

The study aims to recruit 120 families. The intervention under study is newly developed; hence, we used a meta-analysis testing the overall effect of similar interventions (targeting parental involvement in children’s learning, including “paired reading”) to inform the required sample size. The outcomes used to assess effect sizes in the meta-analysis were a combination of different standardized and unstandardized reading measures. The suggested effect sizes were in the range of *d* = .65 to 1.15 [22]. With α < 0.5, power = 0.80, and expected effect size *d* = .65, the necessary sample size is *n* = 78, with 39 families in each group. Although the Oral Reading Fluency (ORF) test administered in the current trial is similar to the assessments used by the studies in the meta-analysis, none of those studies used the actual ORF test of this trial. Hence, the power calculation lacks some precision. To account for uncertainty in the power calculation, subgroup analyses (of gender, site, and CWS measure), and possible study dropouts, and to compensate for the possibility of non-normal distribution of scores, more participants than deemed necessary according to the power calculation were recruited. Based on information from the participating CWS agencies about their target groups, this sample size seems attainable.

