### Measures

The primary implementation measures are related to intervention fidelity (adherence to core components, parent comprehension of core components, and user satisfaction with delivery of intervention components). Primary effectiveness outcomes are reading and math scores and parental involvement in school. The ORF test has two subscales: a fluency score and an accuracy score. A composite variable of the two reading outcomes will be made.

Secondary outcomes (and covariates) are measures of intervention feasibility, acceptability, and appropriateness; practitioners’ perceived competence in providing academic support; and children’s mental health and adjustment, social skills, and executive functioning. The theoretical implementation model is shown in Fig. 2.

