### Statistical analyses

We will consider efficacy for each of the primary outcomes. In other words, efficacy will be gauged in an outcomes-specific manner. A significance level of .05 will be used.

Outcomes will be evaluated using analysis of covariance (ANCOVA), controlling for baseline scores and covariates. Children’s age, implementation drivers, children’s mental health, social skills, and executive functions will be tested in regression models, as will possible subgroup analyses. To test for indirect effects (or mediation), models will be tested in a structural equation modeling (SEM) framework. Indirect effects variables include PASS, Five-to-Fifteen , and the end-of-intervention checklist measures. Implementation drivers as predictors of outcomes will be tested in regression models. We will evaluate effectiveness in two parts. The pre-post outcome analysis will use ANCOVA with baseline measures and covariates as control variables. We will test intervention effects including all data waves in SEM. See Figs. 2 and 3 for the theory of intervention change depicting variables included in the analyses.

We will examine and present data both in intention-to-treat (ITT) and as-treated (AT) designs, as the two approaches answer different questions. An ITT design answers the question “Does the intervention make a difference?” An AT analysis, on the other hand, answers the question “What are the effects likely to be if the client (or family) is exposed to the intervention?” We consider both of these questions important. This procedure has been recommended as best practice [46].

We will use multiple imputation for missing values for the pre-post ANCOVA in an ITT design. In the SEM models, missing data will be estimated using full information maximum likelihood.

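### The printed alpha of 0.5 in the power calculation is wrong (78 holds at two-sided .05), and three primary effectiveness outcomes are each tested at .05 without adjustment

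*Protocol article*

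**What the plan says.** The Power calculation section gives its inputs as "With α < 0.5, power = 0.80, and expected effect size" d = .65. It concludes that 78 families are needed, "with 39 families in each group". The effect size comes from a meta-analysis of reading measures. Recruitment is set at 120, and the excess over 78 is explained by several reasons together: "To account for uncertainty in the power calculation, subgroup analyses (of gender, site, and CWS measure), and possible study dropouts", plus possible non-normality. No dropout rate is given.

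Under Measures: "Primary effectiveness outcomes are reading and math scores and parental involvement in school". The two reading scores are combined into one composite, so there are three primary effectiveness outcomes. Fidelity is a primary implementation measure, but its session checklists are completed only for the intervention group, so it is not a fourth between-group test.

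Under Statistical analyses: "In other words, efficacy will be gauged in an outcomes-specific manner. A significance level of .05 will be used". No multiplicity adjustment is stated. That section also plans a pre-post ANCOVA and an all-waves structural equation model, with both intention-to-treat and as-treated results, and mentions possible subgroup analyses. Under Aims and hypotheses, academic achievement and parental engagement are separate hypotheses. Academic achievement is one hypothesis, measured by reading and math.

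**The concern.** A power calculation should be reproducible from its printed inputs. This one is not: an alpha of 0.5 conflicts with the level under Statistical analyses and cannot lead to 78.

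The second issue is the decision rule. If a positive result on any one of three outcomes were reported as the intervention working, the chance of a false claim would exceed 5%. Two parts of the protocol make such a combined reading possible. The academic-achievement hypothesis has two tests behind it, and the Knowledge translation procedure section says the trial data will feed one overall evaluation that decides between sustaining the intervention and withdrawing it. The power statement covers one outcome at one threshold, and its effect size comes from reading measures only.

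**Working it through.** **Inputs.** From the Power calculation section: d = .65, power .80, 39 per group, 120 families planned (60 per group at 1:1). From Statistical analyses: level .05. From Measures: three primary effectiveness outcomes. Assumed, because the protocol does not state them: two-sided tests, the loss rates, the correlations and equal subgroup splits.

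**1. The plan's own figure.** Normal approximation: n per group = 2(z₁₋α/₂ + z₀.₈₀)² / d². The exact two-sample t-test uses the noncentral t with λ = d√(n/2).

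| Alpha | Normal approximation | t-test | Total (t-test) |
|---|---|---|---|
| .05 two-sided | 2(1.960 + 0.842)²/0.4225 = 37.2, so 38 | 38.1, so 39 | **78** |
| .05 one-sided | 30 | 30.0, so 30 | 60 |
| .5 two-sided | 2(0.674 + 0.842)²/0.4225 = 10.9, so 11 | 10.2, so 11 | 22 |
| .5 one-sided | 4 | 3.4, so 4 | 8 |

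The stated 78 matches exactly at two-sided .05, where power with 39 per group is 80.9%. At alpha .5, 78 families would have 98.6% power. The 0.5 never entered the calculation.

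**2. Chance of at least one false positive.** For k independent tests at .05 it is 1 − 0.95ᵏ. Correlated cases are by simulation from a multivariate normal.

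| Correlation (assumed) | Three outcomes | Reading and math only |
|---|---|---|
| 0 | 1 − 0.95³ = 14.3% | 1 − 0.95² = 9.75% |
| 0.5 | 12.5% | 9.1% |
| 0.7 | 10.9% | 8.4% |

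The three-outcome figures are 2.9, 2.5 and 2.2 times 5%.

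**3. Power per outcome with 120 enrolled.** Unadjusted t-test, d = .65. The first Holm step over three outcomes is .05/3 = .0167.

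| Loss (assumed) | Per group | At .05 | At .0167 |
|---|---|---|---|
| 0% | 60 | 94% | 87% |
| 15% | 51 | 90% | 80% |
| 20% | 48 | 88% | 77% |

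At .0167, 80% power needs 51.01 per group, so 52, or 104 in total. That is within 120 as long as loss stays below about 13% (52/60 = 0.867).

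**4. Subgroups**, at .05, with no loss and no covariate adjustment.
- Half the sample (30 per group): 70%.
- One third (20 per group): 52%.
- A difference of 0.65 in effect between equal halves: standard error √(4/30) = 0.365; 0.65/0.365 = 1.78; power ≈ Φ(1.78 − 1.96) = 43%.

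**The case against.** **The misprint changes nothing numerically.** This stands. A reader might infer that the trial was sized at the wrong alpha, or that the stated power fails to describe it. Neither follows: 78 with 80% power is correct for one outcome at two-sided .05, and outcome-by-outcome testing at .05 is what that calculation assumes.

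**No familywise rate is claimed.** This also stands. The .05 is expressly specific to each outcome, and the protocol nowhere says that one success proves overall efficacy. Whether separately reported hypotheses need adjustment is debated. The argument is weakest for reading and math, which serve a single hypothesis.

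**Near-threefold inflation is the extreme case.** Correct. It holds only for independent outcomes.

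**The power figures ignore the planned ANCOVA.** Fair. Adjusting for baseline raises the effective d to .65/√(1 − ρ²). At assumed baseline-outcome correlations of 0.3, 0.5 and 0.7, power at .0167 with 48 per group is 81%, 89% and 98%. For ρ of 0.5 to 0.7, the subgroup figures become 82–93% (a half), 64–80% (a third) and 54–70% (interaction). The unadjusted figures are therefore a floor, given d = .65, although interaction power stays limited.

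**The protocol does not promise powered subgroups.** Correct. A reader might take the 120 as sized for them, but subgroups are one of several reasons for the margin, no particular power is claimed, and Statistical analyses calls them only possible. Equal thirds is also a simplification, since the agencies differ in size.

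**Conclusion.** Two things hold. First, the alpha printed in the Power calculation section is wrong and contradicts Statistical analyses. It is a reporting error with no effect on the 78. Second, three primary effectiveness outcomes are each tested at .05 unadjusted, which gives about an 11 to 14% chance of at least one false positive (about 8 to 10% for reading and math within the academic-achievement hypothesis). The ranges span assumed correlations from 0.7 down to zero.

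This does not make the stated .05 false, because it is outcome-specific. It does mean that an overall efficacy conclusion resting on any one outcome would not be protected at 5%. Control is affordable within 120 families if d = .65 holds for each outcome. The protocol supports that value from reading measures only, so power for math and parental involvement is unsupported at either threshold. The subgroup point is one of labelling: the margin above 78 does not make those analyses confirmatory.

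**What to change.** 1. In the Power calculation section, change alpha to 0.05 and state that it is two-sided. The 78 stays.
2. Apply Holm across reading, math and parental involvement in the pre-post (6-month) intention-to-treat ANCOVA, named as the analysis that carries the efficacy claim. At minimum, apply it across reading and math for the academic-achievement hypothesis. Wherever no adjustment is made, state that no overall efficacy claim will rest on a single unadjusted outcome.
3. Restate power for 120 families: 94% at .05 and 87% at .0167 with no loss; 88% and 77% with an assumed 20% loss. Note that these are unadjusted t-test figures and that d = .65 comes from reading measures.
4. Label the subgroup analyses exploratory and test them by interaction.

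Cost: no extra families. The strictest Holm step lowers power for a single outcome by about 7 points with no loss (94.2% to 86.9%) and 11 points at 20% loss (88.3% to 77.1%), before any gain from ANCOVA. Holm is more than an edit to wording: it changes the decision rule of a trial that is already recruiting, so it should be recorded and dated before outcome data are analysed.
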